## Abstract

**Background:**

Non-invasive ventilation (NIV) tolerance is a key factor of NIV success. Hence, numerous sedative pharmacological or non-pharmacological strategies have been assessed to improve NIV tolerance. Music therapy in various health care settings has shown beneficial effects. In invasively ventilated critical care patients, encouraging results of music therapy on physiological parameters, anxiety, and agitation have been reported. We hypothesize that a musical intervention improves NIV tolerance in comparison to conventional care. We therefore question the potential benefit of a receptive music session administered to patients by trained caregivers (“musical intervention”) to enhance acceptance and tolerance of NIV.

**Methods/design:**

We conduct a prospective, three-center, open-label, three-arm randomized trial involving patients in the intensive care unit (ICU) who require NIV, as assessed by the treating physician. Participants are allocated to a “musical intervention” arm (“musical intervention” applied during all NIV sessions), to a “sensory deprivation” arm (sight and hearing isolation during all NIV sessions), or to the control group. The primary endpoint is the change in respiratory comfort (measured with a digital visual scale) before the initiation and after 30 minutes of the first NIV session. The evaluation of the primary endpoint is performed blindly from the treatment group. Secondary endpoints include changes in respiratory and cardiovascular parameters during NIV sessions, the percentage of patients requiring endotracheal intubation, day-90 anxiety/depression and health-related quality of life, post-trauma stress induced by NIV, and the overall assessment of NIV.

The follow-up for each participant is 90 days. We expect to randomize a total of 99 participants.

**Discussion:**

As music intervention is a simple and easy-to-implement non-pharmacological technique, efficacious in reducing anxiety in critically ill patients, it appeared logical to assess its efficacy in NIV, one of the most stressful techniques used in the ICU. Patient centeredness was crucial in choosing the outcomes assessed.

**Trial registration:**

ClinicalTrials.gov: NCT02265458. Registered on 25 August 2014.

**Electronic supplementary material:**

The online version of this article (doi:10.1186/s13063-016-1574-z) contains supplementary material, which is available to authorized users.

## Background

Acute respiratory failure (ARF) is the most frequent organ failure in patients in the intensive care unit (ICU) [1]. Among the various respiratory supports, non-invasive ventilation (NIV) allows the administration of a positive pressure of air and oxygen, at a set inspiratory flow and FiO_2_, which unloads respiratory muscles and enables alveolar recruitment. NIV has shown its efficacy in acute or chronic respiratory failure [2] and cardiac pulmonary edema [3] in terms of intubation rates [4, 5], mortality [5], and nosocomial infections [6]. These positive findings have not been so clearly found in de novo ARF, where NIV benefits may be outweighed by the risks of delaying intubation [7, 8], which has been associated with increased mortality [8]. Although NIV offers many undisputable advantages over invasive ventilation, its intolerance is one of its major drawbacks. Also, premature cessation of NIV because of intolerance may lead to intubation in some cases [7–9]. Hence, investigators have searched for means of improving tolerance of the technique by increasing patient comfort. Light sedation has been shown to decrease NIV-induced discomfort [10–13] and appears to be safe and effective, but this alternative remains a pharmacologic intervention requiring the administration of potentially dangerous anesthetic drugs, such as propofol, remifentanil, or dexmedetomidine. Among non-pharmacologic interventions, sophrology, which aims at increasing well-being through differential relaxation, has been assessed with interesting results [14]. However, only a limited number of patients have been evaluated, and the major drawback is the need for patient adherence, a specific caregiver’s training, and the presence of a single person with the patient for an entire 30-minute session, which makes it very dependent on the availability of the team.

Music therapy in health care settings has recently been investigated. In the perioperative setting, it has shown beneficial effects on anxiety, pain, analgesia use, and patient satisfaction [15]. In the ICU, several studies [16–19] and a recent meta-analysis [20] described its effects in terms of anxiety and physiological changes (heart rate, respiratory rate, and blood pressure) in patients on invasive mechanical ventilation. These studies showed that music therapy is feasible in the ICU, with beneficial effects on physiological parameters, anxiety, and agitation.

### Study rationale

As anxiety is one of the major components of NIV discomfort that leads to NIV cessation, we therefore questioned the potential benefit of music therapy as a non-pharmocological adjunct to NIV to enhance acceptance and tolerance of the technique.

As "music therapy" implies the intervention of a qualified music therapist, we choose to use the term “musical intervention,” which refers to a receptive music session administered to a patient by trained caregivers. To distinguish the potential effect of an isolation from the ICU’s noise and light nuisance, we decided to build a three-arm trial, as performed in invasively ventilated ICU subjects by Chlan et al. [17].

### Study objectives

The primary objective of the present trial is to assess the hypothesis that a musical intervention administered to patients with ARF in the ICU improves NIV tolerance and thereby their comfort and ventilation parameters after 30 minutes of NIV, in comparison to conventional care.

The secondary objectives are to assess musical intervention effect on respiratory comfort and respiratory and cardiovascular parameters during NIV sessions; on NIV failure; on anxiety and agitation during NIV; anxiety/depression and health-related quality of life; post-trauma stress induced by NIV; and on overall assessment of NIV in terms of discomfort, trauma, and satisfaction.

## Methods/design

### Design

Mus-IRA (MUSique pour l’Insuffisance Respiratoire Aigue) is a prospective, multicenter, open-label, three-arm randomized trial. This study is conducted in ICU patients with ARF requiring NIV. Participants are allocated either to an interventional arm or to the control group. A musical intervention is applied during NIV sessions in the first intervention arm. Participants included in the second intervention arm undergo sight and hearing isolation (sensory deprivation). Participants included in the control arm receive conventional treatment associated with NIV.

### Definitions

“Non-invasive ventilation” refers to a bilevel positive pressure ventilation applied via a non-invasive interface (a face mask); “music intervention” refers to a receptive music session administered to a patient by trained caregivers; “respiratory comfort” refers to a “0” rate on a 10-cm dyspnea visual analog scale; “NIV intolerance” refers to the need for the premature cessation of an NIV session; “NIV failure” is defined by the need of endotracheal intubation.

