### Study population

Eligible patients are adults (≥18 years of age), admitted to the ICU for ARF or exhibiting an ARF during their ICU stay, for whom the physician in charge considers that NIV is indicated.

In each participating ICU, NIV-treated patients are screened for eligibility by the staff members (investigators) 24 hours a day, 7 days a week.

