#### NIV conduction in all three groups

NIV is initiated according to standards of care and in line with each participating ICU’s practices. The detailed NIV protocol is given in Additional file 1. Briefly, masks are chosen according to the patient's morphology, and the physician in charge, along with the nurse and the nursing assistant, initiates the first session.Ventilator settings

Initial ventilator settings are chosen to maximize the patient's tolerance and minimize air leaks, in order to obtain a respiratory rate between 15 and 25 cycles per minute, an exhaled tidal volume of 6–10 ml/kg of predicted body weight, and the disappearance of signs of respiratory distress. FiO_2_ is set to obtain a minimal pulse oximetry of 92 %. The duration of NIV sessions is left to the discretion of the physician in charge, based on the patient’s needs.Subsequent NIV sessions

The subsequent NIV sessions are conducted by the nurse and nursing assistant according to a prespecified timeline: the physician in charge prescribes the length of NIV sessions and the number per day.Patient monitoring during NIV sessions

All patients undergo careful monitoring to detect and treat any complications related to ARF or NIV. Criteria for intubation are those in use in the participating ICUs [23].

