## Data collection and follow-up

Collected data at each time are summarized in the SPIRIT schedule of events shown in Table 1.

**Table 1 Tab1:** Summary of collected data at each time point according to SPIRIT 2013 guidelines

			Study period							
	Enrollment	Allocation	Post-allocation — at each NIV session						NIV discontinuation, ICU discharge or day 28	Close-out Day 90
Time point			*t* _1_ beginning of NIV session	*t* _2_(*t* _1_ + 5 min)	*t* _3_(*t* _1_ + 30 min)	*t* _4_(*t* _1_ + 1 h)	*t* _*x*_ ^a^	End of each NIV session		
Enrollment:										
Eligibility screen	X									
Informed consent	X									
Allocation		X								
Interventions:										
Musical intervention										
Sensory deprivation										
Control group										
Assessments:										
*Baseline variables:* Demographic data and medical history, SAPS III, SOFA	X									
*Outcome variables:* Respiratory comfort, RASS			X	X	X	X	X	X		X
Respiratory and hemodynamic parameters		X	X	X	X	X	X	X		
*Ongoing therapies:* Catecholamine infusion, need for ETI, attempts to pull out NIV mask, headphones or sensory isolation, need for physical contention, sedative or anxiolytic treatments, NIV complication		X						X		
Health-related quality of life (HADS and SF-36 scores)		X								X
Length of ICU and hospital stay										X
Vital status, NIV satisfaction, comfort and associated trauma, IES-R for NIV									X	X
Decision to withhold life-sustaining therapies									X	

*NIV* non-invasive ventilation, *ETI* endotracheal intubation, *HADS* Hospital Anxiety and Depression Scale [28], *IES-R* Impact of Event Scale - Revised [31], *RASS* Richmond Agitation-Sedation Scale [30], *SAPS III* Simplified Acute Physiological Score III [26], *SF-36* Short Form-36 [29], *SOFA* Sequential Organ Failure Assessment [27]

^a^
*t*
_*x*_ stands for *t*
_1_ + 2, 3, 4, 6, 8, 12, 16, 20, 24 hours depending on the length of each NIV session

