Apart from endotracheal intubation, the need for tracheostomy during the ICU stay and vital status at ICU discharge are recorded. Patients are surveyed for numeric scaling of NIV satisfaction, NIV comfort, and NIV-associated trauma. The Impact of Event Scale - Revised (IES-R) [31] is applied to NIV.

### At day 90

Vital status is regularly updated for each patient until the end of the study. In order to determine the 3-months health-related quality of life, numeric scaling of NIV satisfaction, NIV comfort, and NIV-associated trauma, the IES-R applied to NIV, and the HADS questionnaire [28] and SF-36 [29] are determined and recorded by a blinded-to-randomization group research staff member through a phone survey of patients who are alive.

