##### Percentage of patients requiring physical restraints or administration of anxiolytics or sedatives during NIV sessions, percentage of intubated patients

These percentages will be compared between groups by the usual tests for comparing proportions.

##### SF-36, HADS scores, IES-R scores, and overall assessment of NIV between inclusion and day 90

The evolution of these scores between baseline and day 90 (difference between the measurement at 3 months and inclusion) will be compared between groups by the usual tests comparing continuous variables.

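### NIV failure is analysed as intubation alone, so a patient who dies without being intubated is counted as a non-failure on this secondary endpoint

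*Protocol article*

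**What the plan says.** All references are to the protocol article.

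- **Objective and definition.** Study objectives lists NIV failure among the secondary objectives. Under Definitions, NIV failure "is defined by the need of endotracheal intubation".
- **Endpoint.** Secondary endpoints repeats this as a percentage of patients requiring intubation, and ties it to the end of an NIV session. No item in that list includes death.
- **Analysis.** The matching heading in Statistical methods speaks of the "percentage of intubated patients". Below it: "These percentages will be compared between groups by the usual tests for comparing proportions".
- **Who can enter.** Study population admits adults with acute respiratory failure "for whom the physician in charge considers that NIV is indicated". Inclusion and exclusion criteria adds a minimum level of consciousness. Being a candidate for intubation is not required. The single end-of-life criterion joins two conditions: a decision to withdraw life-sustaining treatment, and an expected survival below 48 hours.
- **What is collected.** Table 1 has a row "Decision to withhold life-sustaining therapies", marked at NIV discontinuation, ICU discharge or day 28. In the text for that same time point, the need for tracheostomy and "vital status at ICU discharge are recorded". Vital status is collected again at day 90.
- **Intubation criteria.** NIV conduction in all three groups: "Criteria for intubation are those in use in the participating ICUs".

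**The concern.** Intubation can be observed only in a patient who is a candidate for it and who lives long enough. Death without intubation is therefore a competing event. Under the planned analysis that patient stays in the denominator and is absent from the numerator, exactly like a patient who recovered on NIV.

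The endpoint matters because it is the clinical outcome in the list closest to whether NIV worked. The Background itself says that in de novo respiratory failure "NIV benefits may be outweighed by the risks of delaying intubation", and that such delay has been associated with higher mortality. A lower intubation percentage is good news only if it is not accompanied by more deaths without intubation, and the endpoint as defined cannot tell the two situations apart.

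**Working it through.** **1. The plan's own figure.** There is no sample size or expected rate for NIV failure. The only design figure is for the primary endpoint: standardised difference 2/2.5 = 0.8, 80% power. The two-sample t calculation gives 25.5, so 26 per arm, at two-sided 5%, and 30.99, so 31 per arm, at 2.5%. Allowing for 5% loss, 31/0.95 = 32.6, so 33 per arm and 99 in total. This reproduces the plan and does not depend on how NIV failure is defined. The 33 per arm is used below only as a denominator.

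**2. Following one patient through the text.** Take a patient for whom intubation has been ruled out, with no withdrawal decision.
- Eligibility: NIV is judged indicated and the two-part exclusion is not met, so the patient can be randomised.
- Course: the patient dies without intubation.
- Analysis: the patient is not among those intubated, so is a non-event, and no other listed endpoint registers the death.

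The same holds if the limitation is decided after randomisation, or if a withdrawal decision exists with longer expected survival.

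**3. Effect on the overall level (assumed rates).** Let s be the share of patients with a do-not-intubate limitation and d the proportion of them who die without intubation. Assume 30% intubation in the other patients and none in those with a limitation.
- Intubation only = (1 − s) × 0.30
- Intubation or death without intubation = (1 − s) × 0.30 + s × d
- Deaths counted as non-failures, out of 99 = 99 × s × d

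| s | Intubation only | Composite, d = 20% to 60% | Deaths counted as non-failures |
|---|---|---|---|
| 5% | 28.5% | 29.5% to 31.5% | about 1 to 3 |
| 10% | 27.0% | 29.0% to 33.0% | about 2 to 6 |
| 20% | 24.0% | 28.0% to 36.0% | about 4 to 12 |
| 30% | 21.0% | 27.0% to 39.0% | about 6 to 18 |

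The gap between the two definitions is s × d, here 1 to 18 percentage points.

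**4. Effect on the comparison (assumed counts, 33 per arm).**
- Intubated: control 8/33 = 24.2%, music 5/33 = 15.2%, a difference of 9.1 points.
- Add deaths without intubation, 1 and 4: (8 + 1)/33 = 27.3% and (5 + 4)/33 = 27.3%, no difference.
- Neither contrast would be significant: Fisher p = 0.54 for 8 versus 5, and p = 0.36 for 1 versus 4. The example shows the direction of the distortion and is not a forecast.

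**5. Chance imbalance alone.** With 30% intubation among candidates in both arms and no treatment effect, 3 versus 8 do-not-intubate patients gives 30 × 0.30/33 = 27.3% versus 25 × 0.30/33 = 22.7%.

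**The case against.** Several points on the other side have force.

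- **Deaths are not concealed.** Vital status is collected, and the opening of Statistical analysis promises numbers and percentages for qualitative variables by group at each assessment date. Deaths should therefore appear by arm. This stands, and it means the plan would not simply report benefit while mortality went unseen. A descriptive table of all deaths, however, does not correct the tested proportion or show who died without intubation.
- **The wording is about need.** Definitions, Secondary endpoints and Table 1 refer to needing or requiring intubation, which could cover a patient who meets criteria but is not intubated because of a limitation. This is a real ambiguity. The article does not adopt that reading, leaves the criteria to each unit, and heads the analysis with patients intubated.
- **Randomisation balances limitations at entry in expectation.** True. Systematic distortion needs a difference between arms in deaths without intubation; otherwise only chance imbalance and a lower overall level remain.
- **The mechanism is speculative.** The Background's warning concerns de novo respiratory failure, and nothing in the article shows that 30 minutes of music delays intubation. This stands.

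Three stronger readings are tempting but unsupported. A reader might say that such a patient is scored as an NIV success, but the article has no success category; non-failure is the accurate term. A reader might take the Table 1 row as proof that patients with limitations at entry are expected. That row is marked only after randomisation, so their eligibility is inferred from the narrow exclusion. A reader might also conclude that intubation between sessions is ignored. That rests on one loose phrase in Secondary endpoints; Definitions and the analysis heading have no such restriction, and intubation is also mentioned among the items recorded at NIV discontinuation, ICU discharge or day 28.

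**Conclusion.** The point holds in a limited form. As analysed, NIV failure is the percentage intubated, death enters no listed endpoint, and the exclusion criteria leave room for patients who will not be intubated. A patient who dies without intubation is therefore counted as a non-failure, and a between-arm difference in such deaths would distort the comparison.

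The size cannot be established from the documents, which give no rates for treatment limitation, intubation or death. The 1 to 18 point gap and the 9-point example rest wholly on assumed values. The consequence is confined to one secondary endpoint with no power calculation. The primary endpoint, its test procedure and the 99-patient sample size are untouched. This is a worthwhile, inexpensive improvement and not a flaw in the trial's main conclusion.

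**What to change.** 1. Define NIV failure as endotracheal intubation at any time, or death without intubation, from randomisation to ICU discharge or day 28, stating which of the two closes the window. Remove the end-of-session qualifier from Secondary endpoints, and use the same definition there, in Definitions and in the analysis section.
2. Report intubation and death without intubation separately by arm beside the composite, so the intubation percentage remains visible.
3. If a supporting analysis by treatment limitation is wanted, base it only on decisions in place before randomisation. A subset defined by later decisions would condition on something that treatment could influence, in an open-label trial. This needs the timing of the decision to be recorded, which the article does not list.

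**Cost.** Items 1 and 2 need revised wording and one extra table, from data already collected. Item 3 needs one added field. The downside is small: the composite will include some deaths unrelated to NIV tolerance, which is why the components should be shown. No eligibility criterion or clinical rule changes.

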### Ethical aspects

The ethics committee of the French Society for Intensive Care Medicine (Commission d’Ethique de la Société de Réanimation de Langue Française approval CE SRLF 14–21) and the competent French authorities (Comité de Protection des Personnes d’Île de France IV, Hôpital Saint-Louis; registration number 2014-A00643-44; date of approval 26 March 2015) approved the study protocol and patient information documents. According to French law on interventional studies, the patient’s (or his next of kin’s) written informed consent is mandatory for inclusion and randomization.

### Participating ICUs

The three French participating units (Louis Mourier, Gustave Roussy, and CHD de Vendée) have an expertise in NIV. Nurses and nursing assistants have received music intervention training by a skilled music therapist. All participating ICU staff members have received training in the study procedures and protocols to provide the musical intervention and standardized NIV sessions.

### Study population

Eligible patients are adults (≥18 years of age), admitted to the ICU for ARF or exhibiting an ARF during their ICU stay, for whom the physician in charge considers that NIV is indicated.

In each participating ICU, NIV-treated patients are screened for eligibility by the staff members (investigators) 24 hours a day, 7 days a week.

### Inclusion and exclusion criteria

The inclusion criteria are as follows:Adults (≥18 years of age)For whom the physician in charge considers that NIV is indicatedWith a level of consciousness good enough to benefit from the musical intervention (Glasgow Coma Scale ≥12).

The non-inclusion criteria include:Patients with a classical contraindication to NIVPatients with severe hearing impairmentPatients for whom a decision of withdrawal of life-sustaining therapies has been made, and with an estimated life expectancy of less than 48 hrsPatients included in another trial dealing with an ARF treatment strategy.

### Randomization

Eligible consecutive patients are randomly allocated to one of the three study arms. Randomization and concealment are achieved using a centralized, secure, computer-generated, interactive, web-response system accessible from each study center (CleanWEB, Telemedicine technologies S.A.S, Boulogne-Billancourt, France) [21]. The randomization is balanced by blocks of variable and undisclosed size and stratified on the center and the presence of a chronic respiratory insufficiency. Before randomization, the presence of the inclusion criteria and the absence of the non-inclusion criteria are verified and entered in the electronic case report form. In each ICU, patients are enrolled by the local physicians and a clinical research nurse and/or clinical research assistant. The randomization day is the study day 1.

